#### Measures

Objective 2 includes data extraction from medical records for the following variables: gestational age at identification of symptoms of mental ill-health and gestational age at diagnosis of mental ill-health.

#### Statistical Analysis

For objective 2, survival analysis will be used to assess differences in the timing of mental ill-health identification during pregnancy. Group comparisons will be performed using Cox proportional hazards regression analysis, including an indicator variable for pre- versus postimplementation. The model will be adjusted for potential confounders (eg, age, primiparous women, civil status, employment status, maternity clinic), selected according to the disjunctive cause criterion [38].

The effect measure will be the hazard ratio with 95% CIs.

#### Statistical Power

To evaluate the statistical power of this component of the study, we estimated the MDD based on the expected number of events. Drawing on the prevalence estimates and sample sizes outlined in the section “Estimated Sample Size and Power,” we approximated a total of 142 events across both study groups. Assuming a 2-sided significance level of 5% and 80% statistical power, the study is capable of detecting a hazard ratio of approximately 1.65, based on the method by Schoenfeld [39]. This suggests that the study is sufficiently powered to detect a 65% or greater difference in the rate of identification of mental ill-health between the pre- and postimplementation groups.

### Objective 3

#### Study Design

This pre- and poststudy design will compare the pre- and postimplementation of a program for psychosocial assessment.

#### Participants and Data Collection

Participant inclusion and data collection will be performed according to the description in objective 2.

#### Measures

Objective 3 includes data extraction from medical records for the following variables: whether the patient received psychological or medical treatment for mental ill-health that was initiated prepregnancy, whether the patient received psychological or medical treatment for mental ill-health that was initiated during pregnancy, and referral pathways to other health care providers when mental ill-health is identified.

#### Statistical Analysis

The proportion of patients referred to specific treatments before and after the intervention will be compared using logistic regression analysis. The primary focus will be on changes in referrals to psychological treatment. The regression model will include covariates selected based on the disjunctive cause criterion to adjust for potential confounding factors (eg, age, primiparous women, civil status, employment status, maternity clinic).

The effect measure will be the OR with 95% CIs.

#### Statistical Power

As described in the “Dichotomous Outcomes” subsection of the “Estimated Sample Size and Power” section, the study is powered to detect a change of approximately 4% to 5%, using a 2-sided test with an α level of 5% and 80% statistical power.

### Objective 4

#### Study Design

This pre- and poststudy design will compare pre- and postimplementation of a program for psychosocial assessment.

#### Participants and Data Collection

Regarding objective 4, participant inclusion and data collection have been completed, and data management and analysis are ongoing. Participant inclusion was performed according to the description in objective 2. In the 2 different patient groups, pre- and postimplementation questionnaires were sent twice during pregnancy. The first questionnaire was administered in early pregnancy after the first 2 visits to the midwife, and the second questionnaire was administered after gestational week 33.

#### Measures

The questionnaires covered the following areas: whether the midwife had asked questions about the participants’ mental health, their experience with the maternity clinic visits, whether they had been given support and help, previous psychiatric diagnoses, current mental health, treatment for mental ill-health during pregnancy, fear of childbirth, and self-assessed mental health.

Objective 4 will include questionnaire data for the following questionnaire items:

How is your current mental health? (scale 1-10; 1=very poor, 10=very good)Have you had any psychological or psychiatric disorder diagnosed by a health care professional? (dichotomous response: Yes or No)To what extent do you feel that you received help for your mental health from your midwife? (scale 1-10; 1=not at all, 10=to a high degree)If you had extra visits with the midwife, to what extent do you feel they helped you? (scale 1-10: 1=not at all, 10=to a high degree)Did the midwife refer you to another health care provider? (dichotomous response: Yes or No)How long did it take to get in contact with another health care provider? (number of gestational weeks)

#### Statistical Analysis

Dichotomous outcomes will be analyzed using logistic regression models, while continuous outcomes will be analyzed using linear regression models. The regression model will include covariates selected based on the disjunctive cause criterion, to adjust for potential confounding factors (eg, age, primiparous women, employment status, maternity clinic).

For dichotomous outcomes, effects will be expressed as ORs with 95% CIs. For continuous outcomes, effects will be reported as mean differences, also with corresponding 95% CIs.

#### Statistical Power

As described in the “Estimated Sample Size and Power” section, the study is powered to detect a change of approximately 4% to 5% for dichotomous outcomes using a 2-sided test, with an α level of 5% and 80% statistical power. For continuous outcomes, the study is designed to detect standardized mean differences of approximately 0.15.

### Objective 5

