#### Secondary Objectives

##### Objective 3

The third objective aims to answer: Does a program for psychosocial assessment during pregnancy influence the measures taken within the health care system and collaboration between the maternity clinic, perinatal psychologists, and other health care providers and agencies when mental ill-health is identified?

##### Objective 4

The fourth objective aims to answer: Does a program for psychosocial assessment during pregnancy influence women’s experiences with receiving help and support for identified mental ill-health?

##### Objective 5

The fifth objective aims to answer: What is the experience of midwives and psychologists when working with the program for psychosocial assessment during pregnancy?

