#### Dichotomous Outcomes

The minimum detectable difference (MDD) with this design varies inversely with the pre-implementation prevalence. For instance, it can reliably, with 80% power, discern an 8% change in a 50% pre-implementation prevalence and more refined changes—such as 5% at a 10% prevalence or 4% at a 5% prevalence, with the same power at a higher prevalence (90% and 95%). This makes the design ideal for testing hypotheses expected to result in either a marked increase or decrease in prevalence rates, ensuring accurate detection of both common and rare conditions, as well as self-rated dichotomous factors according to the questionnaire data.

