#### Continuous Outcomes

The study has the capacity to detect minimal standardized differences as small as 0.15 with 80% power. This level of sensitivity is particularly beneficial for hypotheses investigating subtle changes in continuous measures, such as gradual improvements or declines in health measures, psychological scores, continuous variables according to the questionnaire data, or any other continuous outcomes that fall well within the scope of this design. Given these conditions, the study design is suitable for a broad spectrum of hypotheses and can be used effectively to advance our knowledge in this field.

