#### Participants and Data Collection

Pregnant women who could communicate in Swedish and who were enrolled in early pregnancy at maternity clinics in the Västmanland Region were invited to participate in the study. In the poststudy, patients from all 25 maternity clinics in the region were invited to participate. The women were sent an envelope by post with an invitation to participate, a consent form, and a questionnaire. Consent covered the review of medical records (objectives 2 and 3) and questionnaire data (objective 4).

Participant inclusion was completed in 2022. Pre-implementation (2019), a request for participation was sent to 887 patients, and 487 were included. Questionnaire 2 was sent to 512 patients, and 314 responded to both questionnaires 1 and 2. Postimplementation (2020-2021), a request for participation was sent to 2368 patients, and 942 were included. Questionnaire 2 was sent to 837 patients, and 708 responded to both questionnaires 1 and 2.

A review of medical records will be conducted in the specific data system for antenatal and perinatal health care used in the region, to extract data for objective 2.

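### The detectable differences quoted for Objectives 3 and 4 (4–5 points) and Objective 4 (0.15 SD) omit their prevalence condition and do not fit every listed outcome's denominator

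*Protocol article*

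**What the plan says.** All references are to the protocol article.

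- **Dichotomous Outcomes** (under Estimated Sample Size and Power) opens with "The minimum detectable difference (MDD) with this design varies inversely with the pre-implementation prevalence". It then gives three examples at 80% power: 8 points at a prevalence of 50%, 5 points at 10% and 4 points at 5%, with the last two mirrored at 90% and 95%.
- **Continuous Outcomes** says "The study has the capacity to detect minimal standardized differences as small as 0.15 with 80% power".
- **Objective 3, Statistical Power** refers back to the Dichotomous Outcomes section but carries over only the 4–5 points, with no prevalence attached. It quotes no standardized difference.
- **Objective 4, Statistical Power** refers back in the same way: "the study is powered to detect a change of approximately 4% to 5% for dichotomous outcomes using a 2-sided test". The significance level there is 5% and the power 80%. On the scale and time items it adds "the study is designed to detect standardized mean differences of approximately 0.15".
- **Objective 2, Participants and Data Collection**, which Objectives 3 and 4 share, reports 487 and 942 women included. Of the pre-implementation women, "314 responded to both questionnaires 1 and 2"; the post-implementation count is 708.
- **Objective 4, Measures** lists six items. One rates the help from extra midwife visits and is put only to women who had them. Another asks how many weeks it took to reach another provider.

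**The concern.** The power statements for Objectives 3 and 4 read as properties of the study, although the section they cite makes them depend on prevalence. A reader who sees only the objective-level statement would expect a 5-point change to be detectable for any yes/no outcome, including one near 20%, 30% or 50%.

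The 0.15 SD is likewise applied to all continuous items of Objective 4, although some cannot be answered by everyone enrolled.

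The opening sentence of Dichotomous Outcomes also runs against its own examples. The detectable difference rises from 4 to 5 to 8 points as prevalence goes from 5% to 10% to 50%, so below 50% the relation is direct, not inverse.

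At stake is how null results are read. No clear difference in perceived help, referral or waiting time could be taken to exclude small effects when only larger ones were detectable.

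**Working it through.** **Inputs.** Two-sided 5% level and 80% power (Objective 4, Statistical Power). Enrolled women 487 and 942 (Estimated Sample Size and Power). Both-questionnaire responders 314 and 708 (Objective 2, Participants and Data Collection). About 142 identified women in total (Objective 2, Statistical Power). The counts are taken as printed, although the same Objective 2 section reports questionnaire 2 sent to 512 pre-implementation women when 487 were included.

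**Formulas.**
- Standardized difference at 80% power: (1.96 + 0.8416) × √(1/n₁ + 1/n₂).
- Power at a standardized difference of 0.15: Φ(0.15 / √(1/n₁ + 1/n₂) − 1.96).
- Two proportions: power = Φ{[d − 1.96 √(p̄(1−p̄)(1/n₁+1/n₂))] / √(p₁(1−p₁)/n₁ + p₂(1−p₂)/n₂)}, where p̄ is the pooled proportion, solved for the d that gives 80%.

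**Step 1: reproduce the article's figures.** With 487/942 the detectable increases are 4.06, 5.24 and 7.78 points at 5%, 10% and 50%, which round to the printed 4, 5 and 8. The standardized difference is 2.8016 × √(1/487 + 1/942) = 2.8016 × 0.0558 = 0.156. Power at exactly 0.15 is Φ(0.15/0.0558 − 1.96) = 77%. The planned 640/640 gives nearly the same values (3.99, 5.19 and 7.80 points; 0.157 SD).

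**Step 2: remove the prevalence condition.** Power for a 5-point increase with all 487/942 women:

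| Pre-implementation prevalence | Power for 5 points | Detectable increase at 80% power |
|---|---|---|
| 10% | 76% | 5.2 points |
| 20% | 57% | 6.7 points |
| 30% | 48% | 7.4 points |
| 50% | 44% | 7.8 points |

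For the 50% row: p₁ = 0.50, p₂ = 0.55 and p̄ = (487×0.50 + 942×0.55)/1429 = 0.533. The two standard errors are 0.02785 (pooled) and 0.02786. Power = Φ[(0.05 − 1.96×0.02785)/0.02786] = Φ(−0.164) = 43.5%.

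**Step 3: outcomes that need both questionnaires (314/708).** The standardized difference is 2.8016 × √(1/314 + 1/708) = 2.8016 × 0.0678 = 0.190, and power at 0.15 is 60%. The detectable increases are 5.1, 6.5 and 9.4 points at 5%, 10% and 50%.

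**Step 4: conditional items.** The article gives no count of women with extra visits or with contact to another provider. If the same fraction f of each enrolled group answers, the standardized difference is 0.156/√f. That is 0.59 at f = 7%, 0.49 at 10%, 0.35 at 20% and 0.29 at 30%. Any f below 100% puts it above 0.156.

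**Step 5: identified women only (an assumption).** Ten percent of each group is about 49/94, close to the article's 142 in total. This gives 2.8016 × √(1/48.7 + 1/94.2) = 0.49 SD and a detectable increase of about 24 points at 50% prevalence. If 7% to 30% of those enrolled qualify, the detectable increase at 50% runs from 28 down to 14 points.

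**The case against.** The strongest reply is that the figures are correct where they are derived. The examples in Dichotomous Outcomes reproduce, and both objective-level statements point back to the section that carries the prevalence condition. That stands as a defence of the derivation. It does not rescue the restatement, which drops the 8-point example and presents the most favourable range as general.

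The difference between 0.156 and approximately 0.15 is near rounding. That also stands. It would not merit a comment alone, although Continuous Outcomes does claim 80% power at a value as small as 0.15, where power is 77%.

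Three stronger readings are tempting, and the article does not support them:

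- **That all of Objectives 3 and 4 concern only identified women.** The question in Secondary Objectives is about "experiences with receiving help and support for identified mental ill-health", and the referral measure in Objective 3 is worded similarly. But no section restricts the analyses that way. Two of the three Objective 3 measures and four of the six Objective 4 items carry no such condition. Over all 1,429 women at 5–10% prevalence, 4–5 points for Objective 3 stands.
- **That the identified group is 34 and 94 women.** Applying 7% and 10% to the enrolled numbers gives 34.1 + 94.2 = 128, not the article's 142. The larger figures from that split (0.56 SD, 26 points) are therefore not the plan's own implication.
- **That Objective 4 as a whole has only 314/708 women.** The article does not say which questionnaire supplies which item. Items from the first could keep up to 487/942.

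The estimates will also be reported with 95% confidence intervals, which show the precision achieved. That softens the risk of misreading but does not make the stated power right.

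**Conclusion.** The point holds in limited form. Without any assumption about denominators, the unconditional 4–5 points for Objectives 3 and 4 conflicts with the article's own 8 points at 50%, and the sentence on how detectability varies with prevalence is backwards below 50%.

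For continuous outcomes, which concern Objective 4 only, the best case is 0.156 SD, rising to 0.19 wherever both questionnaires are needed. The extra-visits and time-to-contact items cannot reach 0.15. How far they fall short depends on response counts the article does not give. The figures of about 0.5 SD and 24 points rest on the assumption that only some 142 identified women are analysed.

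These are secondary objectives and recruitment is complete, so this is a correction to stated sensitivity rather than a defect in the design.

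**What to change.** - In the Statistical Power paragraphs of Objectives 3 and 4, give the detectable difference with its prevalence (4 points at 5%, 5 at 10%, 8 at 50%) and name the denominator to be analysed.
- In Continuous Outcomes and in Objective 4, replace 0.15 by 0.16 for outcomes available on all enrolled women and by 0.19 for outcomes that need both questionnaires.
- State that the extra-visits and time-to-contact items can detect only much larger differences.
- In Dichotomous Outcomes, say that the detectable difference is largest at 50% prevalence and falls towards 0% and 100%.

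The cost is a few sentences and no new data. The downside is that the stated figures become less favourable.

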#### Study Design

Focus group interviews will be conducted with an exploratory qualitative design and content analysis.

#### Participants and Data Collection

Regarding objective 5, participant inclusion and data collection have been completed, and analysis will be conducted in the next phase of the study. Participants are midwives who were working in the Västmanland region before, during, and after implementation of the program, as well as those who were employed after the implementation. We have conducted 4 focus group interviews with 3 to 5 midwives in each group, and we also included 1 group with 4 psychologists within maternal and child health care. The participants received verbal and written information and provided written consent.

#### Measures

Data were collected during semistructured focus group interviews based on an interview guide. Questions explore experiences with working with the program and whether the content of the consultation with psychologists and collaboration with other health care providers and agencies changed following the implementation of the program. The interviews were recorded and transcribed verbatim.

#### Data Analysis

Qualitative content analysis with an inductive approach, according to that by Graneheim and Lundman [40], will be undertaken [41,42]. The interviews will be analyzed by the authors. To obtain an overall impression of the data, the transcripts will be read repeatedly. Meaning units will be extracted, condensed, and coded according to relevance to the study aim. The codes will be sorted into subcategories with similar manifest content. The subcategories will be sorted into categories, followed by abstraction and interpretation of both manifest and latent content. The analysis process will be repeated several times and subsequently reviewed by one researcher with extensive experience in qualitative methods in order to ensure trustworthiness.

### Ethical Considerations

This project is carried out in accordance with the latest version of the Declaration of Helsinki and has been approved by the Swedish Ethical Review Authority (permit numbers 2018-331, 2018-332, 2019-02380, 2020-03479, 2020-06902, 2023-01892-02). All data will be managed and securely stored according to the General Data Protection Regulation (GDPR).

All collected materials, including interviews, questionnaires, and medical records will be treated with strict confidentiality and de-identified to protect participant privacy. Data management and storage at the Centre for Clinical Research in the Västmanland Region will strictly adhere to GDPR to ensure security.

Participants were provided information about the study, a consent form, and a questionnaire. Consent was requested to access data from the questionnaire and from medical records. Participants were informed that they had the right to withdraw from the study at any time. The completed questionnaires were sent directly to the Centre for Clinical Research in the Västmanland Region to ensure confidentiality. The review of medical records will be limited to the patient record system for pregnancy and delivery care, which is separate from the general medical records stored in the general system. All participants were informed that their responses would only be reported at a group level, ensuring individual confidentiality.

The participants received a gift card of Sk200 (US $20.91) following completion of the second questionnaire.

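### Diagnosis and treatment in Objectives 2 and 3 are read only from the maternity record while the programme changed what midwives ask, so a pre/post difference could partly reflect recording

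*Protocol article*

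**What the plan says.** **Source.** Under Objective 2, Participants and Data Collection: "A review of medical records will be conducted in the specific data system for antenatal and perinatal health care used in the region". Objective 3 refers back to that description for its own data collection. Ethical Considerations sets the boundary, "The review of medical records will be limited to the patient record system for pregnancy and delivery care", and adds of that system, "which is separate from the general medical records stored in the general system".

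**Outcomes taken from it.** Objective 2 extracts "gestational age at identification of symptoms of mental ill-health and gestational age at diagnosis of mental ill-health". Objective 3 extracts "whether the patient received psychological or medical treatment for mental ill-health that was initiated prepregnancy", then "whether the patient received psychological or medical treatment for mental ill-health that was initiated during pregnancy", and referral pathways to other providers.

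**What the programme changed.** The program description has midwives ask every woman at visit 1 about prior and ongoing serious or perinatal mental illness and treatment. At visit 2 they ask about less serious ill-health, and all women are also asked the Whooley and GAD-2 questions. Under Implementation Strategies, the mental health questions are repeated at week 33. The section on Swedish guidelines says that the 2016 guidance already recommended asking each woman about her mental health in early pregnancy, without stipulating structured identification.

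**What is adjusted for or acknowledged.** The Objective 2 and 3 models adjust for characteristics such as age, parity, civil status, employment and clinic. The missing-data section deals with missing values. The sections on confounders and on limitations name COVID-19, staffing, resources and fidelity, but not a change in recording.

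**The concern.** The guideline section places in-depth assessment and diagnosis with a psychologist or physician, and the referral pathways include general practitioners and psychiatrists. A diagnosis made or treatment given in those settings, if documented only in the general system, is visible to this study only if it also reaches the maternity record. One route is that the midwife asks and notes the answer, and the programme altered that questioning. Ascertainment of the outcome may therefore depend on the exposure.

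The planned models cannot correct this. Covariate adjustment balances who the women are, not how completely their care was noted. The missing-data plan does not reach it either, because a treatment that was never entered would ordinarily be read as no treatment and not as a missing value.

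At stake is the interpretation of the Objective 3 treatment outcomes and of gestational age at diagnosis in Objective 2. A difference in either could be reported as a change in care when part of it is a change in documentation.

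**Working it through.** **1. The plan's own figures.** The sample is 487 women before and 942 after, 1,429 in total, so the pre-implementation share is a = 487/1429 = 0.341. For Objective 2 the plan states 142 events, two-sided 5%, 80% power and a detectable hazard ratio of about 1.65 by Schoenfeld's method:

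- HR = exp[(1.960 + 0.842) / √(142 × 0.341 × 0.659)] = exp(2.802 / 5.648) = exp(0.496) = 1.64.

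This reproduces the stated value. For Objective 3, the detectable differences with these group sizes are 4.1 points from 5% and 5.2 points from 10%, in line with the stated 4% to 5%. These are the yardsticks for a recording artefact.

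**2. Model of the artefact.** Let p be the true proportion treated (or diagnosed), the same in both periods, and let s0 and s1 be the shares of those events that reach the maternity record before and after.

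- Recorded proportion = p × s
- Apparent OR = [p·s1/(1 − p·s1)] / [p·s0/(1 − p·s0)]
- Apparent HR = ln(1 − p·s1) / ln(1 − p·s0)

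The article gives no capture figures, so s0 and s1 are assumptions. I take p = 10%, which matches the plan's event count (0.10 × 1429 = 142.9).

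**3. Worked case.** With 60% against 80%, recorded proportions are 0.10 × 0.60 = 6% and 0.10 × 0.80 = 8%. OR = (0.08/0.92) / (0.06/0.94) = 1.36, with no true change.

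**4. Range.** The last column is the chance of a significant two-sided two-proportion test at 487 against 942 when nothing has truly changed.

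| Capture before / after | Recorded | Apparent OR | Apparent HR | Chance of p < 0.05 |
|---|---|---|---|---|
| 90% / 95% | 9.0% / 9.5% | 1.06 | 1.06 | 0.05 |
| 60% / 70% | 6.0% / 7.0% | 1.18 | 1.17 | 0.10 |
| 80% / 95% | 8.0% / 9.5% | 1.21 | 1.20 | 0.15 |
| 70% / 90% | 7.0% / 9.0% | 1.31 | 1.30 | 0.25 |
| 60% / 80% | 6.0% / 8.0% | 1.36 | 1.35 | 0.27 |
| 60% / 95% | 6.0% / 9.5% | 1.64 | 1.61 | 0.63 |

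A small gap in capture does nothing. Only a jump as large as 60% to 95% produces an apparent HR near the 1.65 the study is powered to detect. The intermediate cases give differences of 1 to 2 points, below the 4 to 5 points for which Objective 3 is powered, though they would still shift the point estimates.

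**5. Where the mechanism bites.**

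| Outcome | Depends on recording of care given elsewhere? |
|---|---|
| Gestational age at symptom identification | No. Earlier identification in maternity care is the intended effect |
| Gestational age at diagnosis | Yes, when the diagnosis is made outside maternity care |
| Treatment begun before pregnancy | Yes, and visit 1 now asks about it directly for serious or perinatal illness |
| Treatment begun during pregnancy | Yes, but no routine question about it after visit 1 is described |
| Referral made by the midwife | Less so. It is plausibly noted in both periods |

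**The case against.** Several points against the concern have force.

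- **The questioning changed less than it may appear.** Treatment is named only at visit 1, and only with serious or perinatal illness. Visit 2 and the week-33 repeat are not described as asking about treatment, so the documented change bears mainly on prior and already ongoing treatment. The earlier period was not silent either, since guidance already recommended asking each woman. This stands, and it limits the likely size.
- **The main analyses lie elsewhere.** Objective 2's question, Cox analysis and power concern identification. Objective 3's primary focus is referral to psychological treatment, often the midwife's own act. This also stands. The concern attaches to diagnosis and treatment, which are nevertheless listed as outcomes to be extracted.
- **Direction is not fixed.** A reader might infer that the error must favour the programme. More complete recording afterwards would inflate treatment overall, but better history-taking could also move women from treatment begun during pregnancy to treatment begun before it, which works the other way.
- **Size is assumed.** A reader might infer that improved recording *would* be reported as more treatment or earlier diagnosis. Without capture figures, the documents support only *could*.
- **Self-report is imperfect.** The wording of the treatment question is not shown. Both questionnaires were answered by 314 of 487 (64%) before and 708 of 942 (75%) after, so completeness itself differs by period. Self-report should therefore not overrule the record.

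None of these supplies a step that separates recording from care.

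**Conclusion.** The concern holds in a limited form. The diagnosis and treatment outcomes are confined to one record system, the programme changed part of the questioning that feeds it, and no adjustment, missing-data step or stated limitation deals with the consequence. A pre/post difference in these outcomes could therefore partly reflect recording.

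The bias could be anything from negligible (OR 1.06 at 90% against 95% capture) through moderate (OR 1.36 at 60% against 80%) to as large as the effect the study is designed to detect (HR 1.61 at 60% against 95%). All of this assumes a true 10% in both periods and capture values that the documents do not give. It does not extend to symptom identification and is weaker for midwife referrals. The point deserves action before the record extraction planned for 2025-2026.

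**What to change.** 1. **Define and word the outcomes for what they are.** State diagnosis and treatment in Objectives 2 and 3 as *documented in the maternity record*, and phrase the conclusions the same way.
2. **Cross-check against data already collected.** The questionnaires, sent in both periods, covered "treatment for mental ill-health during pregnancy" and asked whether the midwife had referred the woman to another provider. Consent covers both records and questionnaires. Link the two and report, by period, the share of self-reported treatment and of self-reported referral that the record captures. Present the self-reported pre/post comparison as a prespecified sensitivity analysis, not as a veto on the record-based result.
3. **Use prepregnancy-initiated treatment as a negative control.** The programme cannot cause treatment that began before pregnancy. A rise there would point to changed recording or to a secular or COVID-19 trend, and should temper the reading of treatment begun during pregnancy.

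The cost is some extra analysis, with no new data collection. The limits are recall error in self-report and restriction to questionnaire responders (314 of 487 and 708 of 942 answered both).
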